### Composition of the data monitoring committee, its role, and reporting structure

The research management group will take on the responsibility of data monitoring. Although we acknowledge that an independent committee would be optimal for this role, financial constraints have made it unfeasible to appoint one. However, as mentioned earlier, stringent research governance procedures are in place at Zhenjiang Mental Health Center to ensure the quality of study conduct.

### Adverse event reporting and harms

tDCS is considered to be a safe technique, but some small risks are recognized. A checklist of potential adverse effects associated with t-DCS administration will be generated with reference to the available literature [28, 29]. All potential risks will be fully disclosed to the participants, along with instructions on how to handle any side effects they may experience. Furthermore, participants will receive a debriefing at the conclusion of each session and will be instructed to contact the principal investigator in the event of any adverse effects resulting from their involvement in the study. In the event of a serious adverse reaction during treatment sessions, local staff (clinic, hospital, institutional) will be promptly notified and emergency protocols will be implemented. We do not expect any adverse events, whether serious or otherwise. However, in the event that one does occur, it will be documented and reported to the local ethics committee of Zhenjiang Mental Health Center.

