### Results from our pilot study

A pilot study [14] was conducted by our team in 39 adults who have MDD with ADS received five consecutive daily sessions of 20-min active or sham HD-tDCS interventions weekly for 2 weeks. The results revealed that the HD-tDCS has significant efficacy in the treatment among MDD patients with anxious distress. The rate of adverse events(e.g., itching, tingling and headache) showed no significant differences between the two groups. Additionally, no severe adverse events or mania was reported. Nevertheless, it should be noted that the trial was of short duration, limited to hospitalized patients, and did not include an evaluation of cognitive or daily functioning. A double-blinded randomized controlled trial (RCT) with an adequate sample size and adequate study periods is warranted to confirm the efficacy of HD-tDCS as an augmentation therapy with antidepressants in MDD patients with ADS.

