#### Adverse effects and risk indicators

The Young Mania Rating Scale (YMRS) [27] will be utilized to detect treatment-induced manic or hypomanic episodes, an 11-item observer-administered scale of mania intensity. YMRS ranges from 0 to 60, with higher scores indicating greater severity. The minimum score required to define a new-onset mania or hypomania is 8 points. A checklist of potential adverse effects associated with the administration of HD-tDCS will be compiled based on available literature [28, 29]. The checklist (Additional file 2) will be utilized to monitor the tolerability and adverse events in each session throughout the intervention. The assessment of risk indicators, such as suicidal ideation or severe self-neglect, will be conducted directly to determine the need for immediate changes in treatment based on identified risks and needs.

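### After the last session, non-manic medical events reach the trial mainly through an instruction that makes the participant judge cause first; separately, the statement that no adverse events are expected contradicts the pilot

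*Protocol article*

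**What the plan says.** **Self-initiated reports.** In the protocol article, Adverse event reporting and harms, participants "will be instructed to contact the principal investigator in the event of any adverse effects resulting from their involvement in the study".

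**Expectation.** The same section opens with "tDCS is considered to be a safe technique, but some small risks are recognized" and later states "We do not expect any adverse events, whether serious or otherwise". The sentence after that commits the team to record any event that does occur and to pass it to the local ethics committee.

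**Pilot.** Results from our pilot study reports: "The rate of adverse events(e.g., itching, tingling and headache) showed no significant differences between the two groups". It continues: "Additionally, no severe adverse events or mania was reported".

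**Solicited collection.** Under Adverse effects and risk indicators, a checklist "will be utilized to monitor the tolerability and adverse events in each session throughout the intervention". The description of the active arm adds a query about discomfort after each stimulation, and the sham procedure is the same apart from the current. Adverse event reporting and harms adds a debriefing after each session. The YMRS is used to detect mania or hypomania, and risk indicators such as suicidal thoughts are assessed directly.

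**Schedule.** In Table 1 the adverse-effects block marks the YMRS at screening, T1, T2 and T3, and the adverse checklist at T1 only.

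**Oversight.** On monitoring: "The research management group will take on the responsibility of data monitoring".

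**The concern.** The words of the contact instruction set a causality test, and the participant applies it. Someone who puts an event down to the depression or to the continuing antidepressant has, on that wording, no reason to call. A harms record should take in the event first and have its cause judged afterwards by someone qualified and blind to arm.

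The stakes are moderate. Adverse effects are a listed secondary outcome. The Discussion anticipates an intervention with minimal adverse effects. A serious adverse event is the article's example of a reason to unblind. All three depend on events reaching the team. The investigators monitor the data themselves, and the ethics committee is the only body outside the treating site's staff that the section names as receiving harms. A complete incoming record therefore matters more here than in a trial with an independent committee.

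The expectation sentence is a separate matter. It says that nothing is expected, although the team's own pilot in this population recorded minor effects. It leaves the trial without a stated set of expected effects.

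**Working it through.** The plan gives no adverse-event rate, so there is no figure to reproduce. The check sets the sections side by side.

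**1. Which routes ask about cause?**

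| Route | Where stated | When | Attribution needed? |
|---|---|---|---|
| Checklist | Adverse effects and risk indicators; Table 1 | Each session; marked at T1 only | No |
| Query after stimulation | Interventions, active arm; sham procedure otherwise identical | Each session | No |
| Debriefing | Adverse event reporting and harms | Each session | No |
| YMRS | Table 1 | Screening, T1, T2, T3 | No, but mania only |
| HDRS-17 | Table 1, primary outcome | Screening, T0 to T3 | No, but depressive symptoms only |
| Direct assessment of risk indicators | Adverse effects and risk indicators | Timing not given; no row in Table 1 | No, but psychiatric risk only |
| Contact with the principal investigator | Adverse event reporting and harms | No time limit stated | **Yes** |

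**2. What remains once sessions end?** The first three routes stop with the tenth session. At T2 and T3 the YMRS, the HDRS-17 and any risk assessment cover mania, depressive symptoms and psychiatric risk. None is a general inquiry about medical events. For everything else, such as a new illness, an injury or an admission for a physical cause, the stated route is the last row, the only one that asks for attribution.

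**3. How long is that period?** Treatment lasts 2 weeks and the last assessment is 6 weeks after it ends: 6 / (2 + 6) = 6 / 8 = 75% of the time from the start of treatment to T3.

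**4. Is the expectation sentence consistent with the rest?**
- The pilot recorded itching, tingling and headache, so an expectation of no non-serious events conflicts with it.
- The pilot reported no severe events, so it does not contradict the part about serious events.
- The section's opening recognises small risks, which conflicts with expecting nothing at all.
- The commitment to record and report follows at once, so the sentence is wrong as a premise but removes no event from collection.

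**The case against.** The strongest reply is that most harm capture in this trial does not depend on the patient's view of cause. That stands for the treatment period. Participants attend five days a week and are asked about discomfort each time, so an event between sessions can surface at the next visit. Worsening mood and mania are measured at every follow-up visit. A reader might infer that harms in general are under-counted; the solicited routes rule that out.

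A reader might also infer that reporting is filtered by which arm the patient believes they are in, which would bias the comparison. The mechanism is plausible, but the documents give no event rates, reporting probabilities or data on patients' beliefs about allocation. If both arms attribute alike, events are lost without a systematic difference between arms.

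Nor is the handling of serious events limited to sessions. The sentence about serious reactions during sessions describes an emergency response. The commitment to record and report comes later and carries no session or attribution limit. That commitment still applies only to events the team learns of, so it does not close the follow-up gap.

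Two further replies have some weight. First, an article leaves event definitions, causality grading and reporting timelines to the full protocol. That is accepted, and none of these is raised here. The point rests on the instruction as worded and on a table that the article presents as the schedule for all assessments. Second, the Discussion ties the adverse-effects objective to completion of the intervention. The YMRS at T2 and T3 nevertheless shows that the trial follows harms beyond that date.

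**Conclusion.** The point holds in a limited form. In the 6-week follow-up, non-manic medical events depend mainly on an instruction that asks the participant to settle causality first. Followed as written, it can lose events that the patient does not attribute to the study. The gap covers 75% of the time from the start of treatment to T3. How many events would be lost, and whether the arms would differ, cannot be established from the documents. The conclusion assumes that Table 1 is complete for follow-up visits and that participants take the instruction at its word.

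The statement that no adverse events are expected is contradicted by the pilot and by the opening of its own section. It must be reconciled with both, although it does not restrict what is collected.

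This is an inexpensive improvement to the safety record. It does not affect the primary efficacy analysis.

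**What to change.** 1. In Adverse event reporting and harms, and in the participant instructions, ask participants to report any new or worsened symptom or medical event up to T3, whether or not they think the study caused it.
2. Add a row to Table 1 for one open adverse-event question at the existing T2 and T3 visits, asked in the same way in both arms.
3. Have relatedness judged afterwards by the evaluators, who are already blinded under Randomization, concealment, and blinding.
4. Replace the sentence expecting no adverse events with the effects seen in the pilot: itching, tingling and headache. The article gives no pilot rates, so the list can stand without them; the team may add them from its own data.

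These are wording changes and one table row, with no extra visits. The downside is slightly more event records to review, some of which will prove unrelated. Under the article's own amendment section, changes of this kind go to the local ethics committee if they count as significant.

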### Plans for communicating important protocol amendments to relevant parties (e.g., trial participants, ethical committees)

The local ethics committee of Zhenjiang Mental Health Center will be consulted for approval of significant protocol modifications, such as changes to eligibility criteria, outcomes, and analyses. Upon receipt of approval, the modifications will be formally communicated in written form to relevant stakeholders (such as investigators and trial participants), and the trial record on chictr.org.cn will be appropriately updated.

### Auditing

The principal investigator (PI) ST shall assume responsibility for the ongoing management of the study. The sponsor shall oversee and perform audits on a subset of studies within its clinical research portfolio. The monitoring and auditing activities will be carried out in accordance with the sponsor’s established procedures for monitoring and audit.

## Discussion

In the DSM-5, an ADS has been included for the diagnosis of MDD [30], which is common among MDD patients without comorbid anxiety disorders and correlated with some of their sociodemographic and clinical characteristics [4]. It captures the core symptoms of anxious emotions and cognitions, providing a valuable framework for treatment planning and symptom assessment [4]. The ADS predicts poorer treatment outcomes as shown by higher depression severity, lower remission rates, and greater frequency of antidepressant side effects in patients with MDD on adequate antidepressant treatment; in contrast, the presence of comorbid anxiety disorders did not predict these treatment outcomes [4]. The assessment of anxiety distress according to DSM-5 was found to be significant not only during the acute phase but also in the continuation/maintenance phase of MDD [31]. This simple 5-item specifier holds great potential for clinical utility in the planning and monitoring of treatment for depressed patients; therefore, new and effective interventions beyond pharmacotherapy and psychotherapy are imperative for this subpopulation with heightened illness-associated burden and risks [6].

This randomized controlled trial aims to evaluate the effectiveness of HD-tDCS as augmentation therapy with antidepressants in ameliorating depressive symptoms in MDD patients with ADS. To this aim, the trial compares the effect of HD-tDCS and sham-control HD-tDCS on improving depressive symptoms in addition to the pre-existing antidepressant regimen. The operationalization of depressive symptoms encompasses three levels, specifically the change in depressive symptoms, clinical response, and remission rate as assessed by HDRS-17. The secondary objectives of this study are to evaluate the impact of the intervention on anxiety symptoms, cognitive function, disability resulting from mental disorders, and adverse effects upon completion of the intervention. We also plan to detect any sustained effect by checking the changes at the 2nd week and 6th week after the finished intervention.

The findings of this trial will prove valuable in the management of MDD patients with ADS, as a new safe treatment option is required to alleviate depressive symptoms for those exhibiting inadequate responses to conventional antidepressants. HD-tDCS is anticipated to be efficacious in ameliorating cognitive function and daily functioning, which are frequently compromised in individuals with MDD.

We acknowledge some limitations of the trial. The study was conducted at a single center, and the generalizability of its findings to other regions or ethnic groups may be limited. In our future studies on HD-tDCS, we shall strive to provide a novel medical foundation for treating MDD patients with ADS using HD-tDCS. The duration of the intervention is brief, and currently, the optimal frequency of presentation to patients remains unknown for achieving maximum efficacy. Although the dosage and timing of antidepressants will remain unchanged for at least 2 weeks prior to the study, it is possible that a change in medication may have an impact, potentially leading to an overestimation of the effect by HD-tDCS. Meanwhile, the diversities of clinical profiles may serve as potential confounding factors, including the types of antidepressants utilized, suboptimal treatment response and resistance levels, or duration of depressive symptoms. Therefore, several key questions remain unanswered and warrant further investigation. These include determining whether patient characteristics or other variables have an impact on outcomes and to what extent. Subgroup analysis will be conducted to mitigate the impact of confounding factors and enhance the trial’s validity.

In conclusion, this trial is a pragmatic randomized double-blinded sham-controlled study that seeks to compare the impact of HD-tDCS versus sham HD-tDCS in treating MDD patients with ADS. To our knowledge, this study is the first HD-tDCS protocol of in this patient population and the first to employ detailed measures of anxiety symptoms combined with assessment of cognition and daily functioning, which will also be used in future analyses. The anticipated outcomes of this investigation hold significance, as it will offer a non-pharmacological intervention for this condition with minimal adverse effects.

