### Randomization, concealment, and blinding

The eligibility participants will be randomly assigned to either active or sham HD-tDCS group with a 1:1 allocation. This study will use the Statistical Analysis Software (version 9.3, SAS Institute Inc., Cary, NC, USA) to generate the random allocation sequence. The randomization list will be enclosed in computer-generated opaque envelopes, each labeled with a sequence number on the outside. After the eligible patients have been screened, the researchers will proceed to open the envelopes. The unblinded researchers will create the randomization sequence and allocate participants to treatments. The trained operators responsible for administering HD-tDCS will not be blinded to allocation and, as a result, will be excluded from assessments and data processing. The participants, statisticians, and evaluators will be kept blinded to the treatment allocation. The unblinding process should only be initiated in the event of an emergency, such as the occurrence of any serious adverse events.

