### Sample size calculation

The sample size will be determined using G*Power 3.1, based on the findings of a a tDCS meta-analysis of adult patients with MDD [17]. In this study, active tDCS was found to be significantly more effective than sham tDCS for the reduction of depression severity (Hedges’ *g* = 0.743). For a power of 80% and an alpha level of 5%, a total sample size of 48 patients (24 in each group) is required to detect significant differences between the groups. To account for a 20% drop-out rate, a total of 58 patients (29 in each arm) will be recruited.

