### Demographic data

The participants’ fundamental demographic information, encompassing age, gender, educational attainment, birthplace, marital status, offspring count, financial standing, family history of affective disorders, and household income will be obtained upon enrollment into the study. Details of the subjects’ psychiatric history, including the age at onset of their initial depressive episode, number of relapse episodes, and current medication and dosage, will be documented during the baseline assessment. The medical history and treatment of patients will be evaluated through direct inquiry and confirmed with their electronic health records in the hospital authority.

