### Statistical analysis

Continuous variables will be summarized using the mean and standard deviation measures. Categorical variables will be presented in terms of frequency and percentage. Between-group comparisons will be assessed using the Mann–Whitney *U* test for continuous variables and either the chi-square test or Fisher exact test for categorical variables. The primary outcome will be analyzed based on the intention-to-treat principle, with worst case imputation applied. For repeated continuous outcomes, a mixed linear model will be employed, which includes the interaction between group (active versus sham) and time (baseline, post-assessment, 2-week and 6-week follow-up assessment.

The hypotheses will be tested using unpaired, two-tailed tests at a significance level of 0.05. The software SAS, v.9.4 (SAS Institute Inc.), was utilized.

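### Subgroup analysis is named as the remedy for confounding, but unpooled subgroup comparisons leave chance imbalance in the overall estimate; a short list of prespecified baseline covariates would address it

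*Protocol article*

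**What the plan says.** The limitations paragraph of the Discussion describes differences in clinical profile as potential confounding factors, "including the types of antidepressants utilized, suboptimal treatment response and resistance levels, or duration of depressive symptoms". It closes with a commitment: "Subgroup analysis will be conducted to mitigate the impact of confounding factors", with the further stated aim of strengthening the validity of the trial. It names no subgroups, pooling across strata, interaction test or exploratory status.

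The Statistical analysis section gives two kinds of comparison. The simple tests are unadjusted: "Between-group comparisons will be assessed using the Mann–Whitney *U* test for continuous variables", with chi-square or Fisher tests for categorical variables. For repeated continuous outcomes, "a mixed linear model will be employed, which includes the interaction between group (active versus sham) and time", where the time levels are baseline, post-assessment, and the 2-week and 6-week follow-ups. No prognostic covariate is named.

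Under Randomization, concealment, and blinding, patients are "randomly assigned to either active or sham HD-tDCS group with a 1:1 allocation", and no stratification factor is stated. Among the baseline data, "number of relapse episodes, and current medication and dosage, will be documented during the baseline assessment", together with age at first onset. Resistance level and duration of the current episode are not named there.

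**The concern.** The sentence assigns a task to a method that does not perform it. Splitting patients by, say, antidepressant class produces two smaller active-versus-sham comparisons. If the arms differ by chance on that factor, the overall comparison still carries the difference, because nothing in the split feeds back into it. Each small comparison can also be imbalanced on the other factors.

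There are two practical consequences. The overall estimate gains nothing in balance or precision on the listed factors. The trial also acquires several low-powered tests that the protocol describes in advance as strengthening validity, so a chance finding in one of them could be read as a result with confounding removed. A statistical analysis plan that followed the sentence literally would carry the mistake forward.

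**Working it through.** **Inputs from the protocol.** Standardised effect: "Hedges’ *g* = 0.743". Power 80%, alpha 5%, 48 evaluable patients (24 per arm), 58 recruited (29 per arm), all from Sample size calculation. Two-tailed testing at 0.05, from Statistical analysis.

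**Reproducing the plan's figure.** A two-sample t-test with d = 0.743, alpha 0.05 and power 0.80 needs 23.1, so 24 per arm (48 in total), if one-sided. Two-sided it needs 29.4, so 30 per arm (60). The stated 48 therefore matches a one-sided calculation. That is a separate matter, but it fixes the reference for what follows: two-sided power is 0.71 at 24 per arm and 0.79 at 29 per arm. The recruited number is 48 × 1.2 = 57.6, rounded up to 58.

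**Is chance imbalance plausible?** Take a binary factor present in half the patients (assumed prevalence) and 29 per arm. Comparing two independent binomial(29, 0.5) counts, the arms differ by 20 percentage points or more with probability 0.148, about 15%.

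**Power within a half-size subgroup.** The noncentrality is d × √(n/2), with n per arm and 2n − 2 degrees of freedom, two-sided 0.05. The even split is an assumption.

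| Patients analysed | n per arm in the half | Noncentrality | Power |
|---|---|---|---|
| 48 | 12 | 0.743 × √6 = 1.82 | 0.41 |
| 58 | 14 | 0.743 × √7 = 1.97 | 0.47 |
| 58 | 14.5 | 0.743 × √7.25 = 2.00 | 0.49 |

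**Power of an interaction test.** With equal halves, the standard error of a treatment-by-factor interaction is twice that of the main effect: 2 × √(2/24) = 0.577 SD at N = 48 and 2 × √(2/29) = 0.525 SD at N = 58. An interaction as large as the whole planned effect (0.743 SD) has noncentrality 1.29 or 1.41, and power 0.24 or 0.28. Interaction tests here can only be exploratory.

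**False positives.** The protocol fixes no number of subgroups. Assume three two-level factors, giving six subgroup tests at 0.05.
- Treated as independent: 1 − 0.95⁶ = 0.265.
- All six tests use the same 58 patients and so overlap. Simulation with no treatment effect and three independent 50/50 factors gives about 0.21 to 0.22.
- Testing both halves of a single factor gives about 0.094 by simulation.

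**What adjustment does to the overall estimate.** Assume one 50/50 prognostic factor explaining 25% of the outcome variance, N = 58, no treatment effect. By formula, the standard deviation of the treatment estimate is √(2/29) = 0.263 unadjusted and about √(0.75 × 2/29) = 0.227 adjusted. Simulation gives 0.263 and 0.230, with type I error 5.1% for the adjusted test. A single-subgroup estimate has a simulated standard deviation of 0.324, so the subgroup route is less precise than doing nothing.

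**What adjustment costs if the covariates are useless.** With three covariates explaining none of the variance, power goes from 0.71 to 0.68 at N = 48 and from 0.79 to 0.77 at N = 58. If they explain 10% (assumed), it goes to 0.73 and 0.81. The comparator in each case is an unadjusted two-group test that ignores baseline, not the planned mixed model.

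**The case against.** The strongest reply is that this is one sentence among limitations, and that covariate lists, subgroup definitions and exploratory labels normally belong in an analysis plan that is not shown. That is right about the omissions, and they are not criticised here. The Statistical analysis section says what the mixed model includes, which need not be every term. What stands is the positive statement that subgroup analysis is the means of mitigating confounding.

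Other points also have force. A stratified analysis pooled over strata does adjust for the stratifying factor, so it would be wrong to say that subgrouping can never help; the protocol simply describes no pooling. The neighbouring sentences ask whether patient characteristics affect outcomes, a question that exploratory subgroups can partly serve.

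A reader might infer more than the document supports:
- **That the trial's result would be confounded.** Randomisation protects against systematic confounding. What is left is chance imbalance and precision.
- **That baseline severity is ignored.** Baseline is a time level in the mixed model, so the HDRS-17 score at T0 already enters as a response. The gap concerns the other factors.
- **That adjusting for the T0 score would lift power from 0.71 to 0.75-0.83.** Those figures assume a correlation of 0.3 to 0.5 and compare with a test that ignores baseline. They are not a gain over the planned model and are not relied on here.
- **That a subgroup finding will be presented as the main result.** Nothing says so; the Statistical analysis section governs the primary outcome.

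**Conclusion.** The point holds in a limited form. The Discussion names a method that does not do what it is said to do. Unpooled subgroup comparisons address effect modification and leave chance imbalance in the overall estimate. For the planned effect of 0.743, half-size subgroups have about 41-49% power. Six such tests would carry roughly a 21-26% chance of a false positive; the upper figure assumes independence and the lower allows for overlap. The even split, the number of factors and the share of variance explained are assumptions, because the protocol gives none of them. The planned primary comparison is not invalidated. This is a correctable mis-statement of method that should be put right before unblinding.

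**What to change.** Replace the last sentence of the limitations paragraph, and state the following in the analysis section or analysis plan before unblinding:

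1. Add a short, fixed list of baseline covariates to the mixed model, drawn from what the trial already records or knows, for example antidepressant class (grouped), number of episodes, and inpatient or outpatient setting. Use resistance level or current-episode duration only if they are recorded at baseline. Leave out medication changes after randomisation.
2. Use the T0 HDRS-17 score once. Either keep it as a response in a model with a common baseline mean across arms, or take it out of the response and enter it as a covariate. Adding it as a covariate while baseline remains a time level would use the same measurement twice.
3. Report subgroups only as treatment-by-factor interactions with confidence intervals, labelled exploratory, and do not describe them as control of confounding.

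The cost is wording, with no change to patients, visits or treatment unless resistance level or episode duration has to be added to the baseline form. With 48 to 58 patients the list must stay short: each covariate uses degrees of freedom, and three that turn out not to be prognostic would cost two to three percentage points of power.
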